# Does closed-loop automated oxygen control reduce the duration of supplementary oxygen treatment and the amount of time spent in hyperoxia? A randomised controlled trial in ventilated infants born at or near term

**DOI:** 10.1186/s13063-023-07415-9

**Published:** 2023-06-15

**Keywords:** Closed-loop automated oxygen control, Term infants, Mechanical ventilation, Hyperoxaemia

## Abstract

**Background:**

Ventilated infants frequently require supplemental oxygen, but its use should be monitored carefully due to associated complications. The achievement of oxygen saturation (SpO_2_) targets can be challenging as neonates experience frequent fluctuations of their oxygen levels that further increase the risk of complications.

Closed-loop automated oxygen control systems (CLAC) improve achievement of oxygen saturation targets, reduce hyperoxaemic episodes and facilitate weaning of the inspired oxygen concentration in ventilated infants born at or near term. This study investigates whether CLAC compared with manual oxygen control reduces the time spent in hyperoxia and the overall duration of supplemental oxygen treatment in ventilated infants born at or above 34 weeks gestation.

**Methods:**

This randomised controlled trial performed at a single tertiary neonatal unit is recruiting 40 infants born at or above 34 weeks of gestation and within 24 h of initiation of mechanical ventilation. Infants are randomised to CLAC or manual oxygen control from recruitment till successful extubation. The primary outcome is the percentage of time spent in hyperoxia (SpO_2_ > 96%). The secondary outcomes are the overall duration of supplementary oxygen treatment, the percentage of time spent with an oxygen requirement above thirty per cent, the number of days on mechanical ventilation and the length of neonatal unit stay. The study is performed following informed parental consent and was approved by the West Midlands-Edgbaston Research Ethics Committee (Protocol version 1.2, 10/11/2022).

**Discussion:**

This trial will investigate the effect of CLAC on the overall duration of oxygen therapy and the time spent in hyperoxia. These are important clinical outcomes as hyperoxic injury is related to oxidative stress that can adversely affect multiple organ systems.

**Trial registration:**

ClinicalTrials.Gov NCT05657795. Registered on 12/12/2022.

**Supplementary Information:**

The online version contains supplementary material available at 10.1186/s13063-023-07415-9.

## Background

Term-born infants require respiratory support for a variety of reasons with an overall incidence of mechanical ventilation of 3.6 per 1000 live births [1]. Mechanical ventilation, although life-saving, is associated with complications including chronic lung disease, abnormal neurodevelopment and increased mortality [2, 3]. Late preterm infants (those born between 34 and 36^+6^ weeks gestation) account for the majority of preterm births and, due to the interruption of normal lung development, are more likely to need mechanical ventilation and at higher risk of all forms of respiratory morbidity when compared to term born neonates [4].

Ventilated neonates frequently require supplemental oxygen, but its use must be monitored carefully due to associated complications. Therefore, oxygen saturation levels (SpO_2_) are continuously monitored in clinical practice and used to guide adjustments to the inspired oxygen concentration (FiO_2_), which are traditionally made manually by neonatal practitioners.

Maintaining peripheral oxygen saturation levels within targets can be challenging as neonates experience frequent fluctuations and episodes of intermittent hypoxaemia or hyperoxaemia [5]. Consequently, clinical staff face a considerable burden of work continuously monitoring and responding to changes in SpO_2_ levels due to the frequency of adjustments needed. Compliance with SpO_2_ targets in oxygen saturation ranges has been variable even within the same patient over time, as well as between patients and centres [6].

Closed-loop automated oxygen control (CLAC) systems work through an algorithm comparing the patient’s SpO_2_ readings with the desired setpoint and calculate an updated value for the inspired oxygen concentration (FiO_2_) that is mechanically adjusted without any human intervention. There are several commercially available devices using different algorithms. An example is the Oxygenie software (SLE) that has been shown to be effective in improving compliance with target achievement in preterm infants and preventing hypoxaemia and hyperoxaemia [7]. In a randomised crossover study, using that device we demonstrated that preterm ventilated infants experienced fewer prolonged desaturations during the closed-loop automated oxygen control period and spent an increased percentage of time within their target SpO_2_ range with fewer manual adjustments to the inspired oxygen concentration [8]. In agreement with the above, a meta-analysis including 13 randomised controlled trials [9], concluded that automated oxygen control systems significantly reduced the percentage of time infants spent in hyperoxia (SpO_2_ > 98%) with fewer manual adjustments to the inspired oxygen concentration. A literature review concluded that the inspired oxygen concentration was reduced more rapidly during automated oxygen control when compared to manual oxygen control [10].

Most of the studies assessing closed-loop automated oxygen control included very preterm or low birth weight infants. Yet, more mature infants are also vulnerable to the risks related to oxygen treatment. In a randomised crossover study in ventilated infants born at or above 34 weeks gestation, we demonstrated that CLAC increased the percentage of time spent within the target range (SpO_2_: 92–96%) (*p* = 0.001), reduced the time spent in hyperoxia (*p* = 0.006) and the duration of hyperoxaemic episodes (*p* = 0.001), with fewer manual adjustments to the inspired oxygen concentration (*p* = 0.004) [11]. In addition, the median FiO_2_ requirement was lower during the automated oxygen control period (*p* = 0.014). It is, therefore, possible and our hypothesis that the use of CLAC will reduce the overall duration of oxygen treatment by reducing the time spent in hyperoxia and facilitating weaning of the inspired oxygen concentration.

The aim of this study is to explore if in ventilated infants born at or above 34 weeks of gestation, the use of closed-loop automated oxygen control compared to standard care reduces the overall duration of supplemental oxygen therapy and the time spent in hyperoxia. These are important outcomes related to respiratory morbidity and the complications arising from oxygen treatment. Our primary outcome is the percentage of time spent in hyperoxia (SpO_2_ > 96%). The secondary outcomes of this study are the duration of supplementary oxygen treatment, the percentage of time with an oxygen requirement exceeding thirty per cent, the number of days on mechanical ventilation and the length of neonatal unit stay.

## Methods

This is a non-blinded, superior, randomised controlled trial. Infants are allocated to parallel groups in a 1:1 ratio.

### Setting

A single tertiary neonatal unit at King’s College Hospital NHS Foundation Trust, London, UK. The unit has previous experience on the use of closed-loop automated oxygen control in the context of trials.

### Inclusion criteria

Inclusion criteria are as follows:Infants delivered at or above 34 weeks of gestational age requiring mechanical ventilation.Recruitment within 24 h of initiation of mechanical ventilation.

### Exclusion criteria

Infants delivered before 34 weeks of gestational age.Infants with congenital cyanotic heart disease.Infants on high-frequency oscillatory ventilation (HFOV).Infants who require oxygen saturation targets > 96%, e.g. infants with pulmonary hypertension or pneumothorax.

### Recruitment

Parents or legal guardians of all eligible infants are initially approached by the clinical team taking care of the infant and if they agree, by a researcher. The parents are provided with an information sheet about the study. The researchers answer questions and respond to any concerns in a face-to-face meeting and obtain written informed consent. The study was approved by the Health Research Authority and by the West Midlands-Edgbaston NHS Research Ethics Committee.

### Randomisation

The randomisation sequence is generated by using an online randomisation generator and concealed in sealed opaque envelopes. This is done by a person independent of the research team who is not involved in the study. A member of the research team will enrol participants to their allocation.

### Enrolment

Infants will be enrolled in the study by the research team within 24 h of initiation of mechanical ventilation following parental consent. Infants are randomised to one of the study arms by opening the next envelope.

### Blinding

The study is not blinded. Decisions regarding ongoing care, for example, ventilator settings and interventions such as blood gases and chest radiographs, are made by the clinical team as per the neonatal unit’s guidelines.

### Intervention

At enrolment, participants are randomised to receiving either closed-loop automated oxygen control (intervention group) or manual control of the inspired oxygen concentration. All infants are ventilated using the SLE6000 ventilators and ventilation settings are manually adjusted by the clinical team as per the unit’s protocol. In addition to standard care, infants in the intervention group are connected to the Oxygenie Auto-O_2_ software (SLE). This software uses oxygen saturation levels from the SpO_2_ probe attached to the neonate, which are fed into an algorithm, to automatically adjust the percentage of inspired oxygen to maintain oxygen saturation within the target range. Oxygen saturation readings will be pre- or post-ductal, unless there is a difference between them, and then pre-ductal readings will be used. Manual adjustments including the percentage of inspired oxygen are allowed at any point during the study, if deemed appropriate by the clinical team. No concomitant treatments will be prohibited during the trial.

The nurse-to-patient ratio is according to the unit protocol that is determined on the patient’s acuity.

Infants are studied from enrolment until successful extubation [12]. Infants who fail extubation and require reintubation within 48 h continue in their initial study arm. Therefore, for infants randomised to the intervention group closed-loop oxygen delivery resumes. If an infant is successfully extubated the study will be completed [11] (Fig. 1).

**Fig. 1 Fig1:**
[figure not shown]
Trial flowchart (Protocol v1.2, 10/11/2022)

### Primary outcome measure

The primary outcome measure is the percentage of time spent in hyperoxia (SpO_2_ > 96%).

### Secondary outcomes

The secondary outcomes are the percentage of time spent with an oxygen requirement exceeding 30%, the duration of supplementary oxygen treatment, the number of days on mechanical ventilation and the length of neonatal unit stay.

The order of study events is detailed in the Standard Protocol Items: Recommendations for Interventional Trials (SPIRIT) figure in Fig. 2. A SPIRIT checklist is also provided as an Additional file and the protocol is based on the SPIRIT reporting guidelines [13].

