### Statistical analysis

Data will be compared between infants in the intervention group (closed-loop automated oxygen control) and infants in the control group (manual oxygen control). The data will be assessed for normality; Student’s *t* test will be used for normally distributed data and Mann–Whitney *U* test for skewed data. Categorical data will be assessed using the Fisher two-tailed exact test. The analysis will be undertaken using SPSS software (SPSS Inc, Chicago, IL, USA). Patients’ data will be analysed according to their randomised assignment group. Imputation of missing data will not be performed.

Ventilation settings and oxygen requirements at the beginning of the study will be compared between infants in the intervention group (closed-loop automated oxygen control) and infants in the control group (manual oxygen control). If there are any statistically significant differences indicating different severities of respiratory disease, we will perform subgroup analysis and comparisons between infants with more and less severe lung disease.

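### Oxygen duration, ventilation days and unit stay are compared as raw lengths with no rule for death or transfer, so read literally an early death enters as a short, favourable value

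*Protocol article*

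**What the plan says.** The Secondary outcomes section of the protocol article lists, besides a percentage of time above an oxygen threshold, the duration of supplementary oxygen, "the number of days on mechanical ventilation and the length of neonatal unit stay". These are lengths as they stand, not days free of treatment or times to an event.

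The Statistical analysis section applies one scheme to all continuous data: Student's t "test will be used for normally distributed data and Mann–Whitney" U for skewed data. It adds that patients' "data will be analysed according to their randomised assignment group" and that "Imputation of missing data will not be performed".

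Shorter is the favourable direction. The Background states the hypothesis that "the use of CLAC will reduce the overall duration of oxygen treatment by reducing the time spent in hyperoxia". Oxygen duration also comes first in the question asked by the title, and it is part of the stated aim.

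The article mentions no worst rank, composite with death, censoring, competing-risk method or handling of transfers. Death is not a listed outcome and would appear only through the serious adverse event reporting in the Safety section. The Intervention section ends the study period at successful extubation and names no end for an infant who dies or leaves before that.

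**The concern.** A raw length is a sound measure of benefit only if every infant reaches the end of treatment or stay by recovering. Death and transfer end the length for another reason. An infant who dies on day 2 has two days of ventilation and two days of stay. Those values are complete, so the no-imputation rule does not touch them, and analysis by assigned arm keeps them in. In a Mann-Whitney test they rank with the quickest recoveries; in a t test they lower the mean. A transfer does the same to unit stay.

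Both events are conceivable here. The Background says that mechanical ventilation "is associated with complications including chronic lung disease, abnormal neurodevelopment and increased mortality", and the Setting is "A single tertiary neonatal unit", so some infants may finish their care elsewhere. The Discussion presents the trial as evidence on oxygen duration and length of intensive care stay ahead of routine use. An apparent shortening that came partly from deaths or transfers would be read as benefit.

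**Working it through.** **Inputs from the article.** 40 infants, 1:1, so 20 per arm (Sample size; Methods). Outcomes, tests, analysis set and missing-data rule are as set out above. Death rates, transfer rates and the distribution of the durations are not given, so everything on size below is assumed.

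**The plan's own figure.** The sample size rests on a difference of 4.9 and a standard deviation of 4.7 in FiO2, 90% power and 5% significance (taken as two-sided):

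n per arm = 2 × (1.960 + 1.282)² × (4.7/4.9)² ≈ 2 × 10.51 × 0.920 ≈ 19.3, rounded up to 20, total 40.

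This reproduces. It supplies the 20 per arm but has no other bearing on the durations.

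**Shift in the mean.** Assume the same survivor durations in both arms, log-normal with median 8 days and log-SD 0.6, and deaths spread evenly over days 1 to 3 (mean 2 days).

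- Survivor mean = 8 × exp(0.6²/2) = 8 × exp(0.18) = 9.58 days.
- Each early death replaces 9.58 by 2 on average, a loss of 7.58 days.
- Net excess of two deaths in 20: (2/20) × 7.58 = 0.76 days. This holds for 2 v 0 and for 3 v 1; simulation of 20,000 trials gave 0.77 and 0.75.
- Net excess of one death: (1/20) × 7.58 = 0.38 days.

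**Set against the noise.**

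- Standard deviation = 9.58 × √(exp(0.36) − 1) = 9.58 × 0.658 = 6.3 days.
- Standard error of the difference = 6.3 × √(2/20) = 2.0 days.
- 0.76/2.0 ≈ 0.38 standard errors.

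**Shorter durations.** The Discussion expects ventilation to be relatively short in these infants. With median 3 days and the same log-SD, the mean is 3 × exp(0.18) = 3.59 days, and the shift is (2/20) × (3.59 − 2) = 0.16 days.

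**Effect on ranks.** If k of 20 infants in one arm die before any infant in the other arm reaches its end, and the arms otherwise agree, the chance that an infant from that arm has the shorter length is k/20 + (1 − k/20) × 0.5. For k = 1 to 4 this is 0.525, 0.55, 0.575 and 0.60, against 0.50 with no deaths. With deaths ranked worst it is (1 − k/20) × 0.5, that is 0.475, 0.45, 0.425 and 0.40.

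**Effect on the test.** Simulation of 4,000 trials per row: Mann-Whitney, 20 per arm, no difference among survivors, lengths log-normal (median 10 days, log-SD 0.7), death times exponential with mean 2 days. The last two columns give the chance of a significant result in favour of CLAC.

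| Death rate, CLAC v control | Raw lengths | Deaths ranked worst |
|---|---|---|
| 0% v 0% | 2.1% | 2.5% |
| 10% v 10% | 2.2% | 2.5% |
| 10% v 0% | 6.8% | 0.6% |
| 15% v 5% | 7.4% | 0.5% |
| 20% v 10% | 7.6% | 0.6% |
| 20% v 0% | 16.8% | 0.3% |

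With equal rates there is no material distortion: the two-sided error at 10% v 10% on raw lengths is 5.3%. With unequal rates, raw lengths credit the arm with more deaths. The worst rank does not make the death signal vanish; it turns it round. At 10% v 0% the two-sided rejection rate is about 7.6% under either scoring, but on raw lengths most of it favours the arm with the deaths.

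**The case against.** The strongest reply is that the article never says deaths or transfers are scored as observed short lengths. It condenses a fuller protocol, an analysis plan may exist, and rules for such infants are often placed there. That is right as far as it goes, and a reader should not infer that the investigators have chosen to count death as a good result. What remains is that the article fixes the form of the outcomes, the tests, the analysis set and the missing-data rule. Followed as written, they yield a definite and unhelpful value for an early death; a fuller document would have to change that default, not merely fill a gap.

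Second, a reader might infer that transfer shortens all three durations. That is clear only for unit stay. Oxygen or ventilation time after a transfer may instead be treated as missing and left out, which loses a randomised infant but does not score a short result.

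Third, the distortion needs unequal event rates, and the document gives none. The Background sentence on mortality is general, and the Exclusion criteria remove several groups, including infants with cyanotic heart disease, on high-frequency oscillation or needing higher saturation targets. The 10% to 20% rates in the table are illustrations, not expectations. This stands.

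Fourth, it is tempting to say that with 20 per arm one or two infants settle the answer. The figures do not support that: two excess deaths move the mean by about 0.4 of a standard error.

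The serious adverse event records would show deaths but would not repair the comparison of durations.

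**Conclusion.** The concern holds as a weakness in how three secondary outcomes are analysed. Under the literal rule, an early death, and for unit stay a transfer out, enters as a short and favourable value, and the comparison tilts towards whichever arm has more of these events.

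The size is modest and conditional. A net excess of two early deaths in 20 shifts the mean by about 0.76 days (standard error about 2.0 days) if durations are log-normal with median 8 days and log-SD 0.6, and by about 0.16 days if the median is 3 days. With equal rates there is essentially no effect on error. An excess of two biases the estimate and raises the chance of a misleading significant result somewhat (2.1% to 6.8% at 10% v 0% in the simulation), but does not create significance alone. The primary outcome, a percentage of time, is outside this point. The change is still worth making because oxygen duration leads the title and the remedy is cheap.

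**What to change.** In the Statistical analysis section, for these three outcomes:

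- Count each duration from randomisation.
- For oxygen and ventilation, either give deaths the worst rank, longer than any survivor, in a Mann-Whitney test that is used whatever the normality check shows, or analyse days alive and free of oxygen or ventilation to a fixed day named in advance, with death scored 0. Choose one beforehand. They are related but not identical, because the second ties deaths with survivors still treated at that day.
- Treat unit stay in the same way.
- For infants transferred out, obtain the end dates from the receiving unit. Use censoring at transfer only as a fallback, because transfer may depend on the infant's condition and so be informative.
- Report deaths by arm beside these outcomes, and the survivors' raw durations descriptively.

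The cost is a few sentences and a request for a few dates; recruitment, treatment and sample size do not change. The downside is that each result becomes a composite with death and no longer describes duration alone, which is why the survivors' raw durations should be shown as well.

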**Fig. 2 Fig2:**
[figure not shown]
SPIRIT figure of trial interventions and timings

### Sample size

In an interim analysis of data from a randomised crossover study on CLAC in ventilated infants born at or above 34 weeks of gestation that was undertaken in our unit, the use of a closed-loop oxygen system was associated with a reduction in the mean FiO_2_ delivery during hyperoxia from 29.6% (manual oxygen control period) to 24.7% (automated oxygen control period, *p* = 0.018), that is a difference of 4.9%. The standard deviation for the FiO_2_ requirement of the infants at the beginning of the automated oxygen control period was 4.7% [14]. Randomisation of 40 infants allowed to detect a difference in the mean FiO_2_ delivery during hyperoxia of 4.9% with a 90% power at the 5% significance level [15].

At the request of the Ethics committee, an interim analysis will be carried out after half the sample have been recruited to review if enough data have been gained at that point. The analysis will be performed by an independent researcher not involved in the project to avoid introducing bias to our data. The research team will be blinded to the results of the interim analysis unless there are any significant findings.

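### The only power calculation is for mean FiO2 delivered during hyperoxia, which is not a listed outcome, so the protocol gives no supported power for its primary outcome (percentage of time with SpO2 > 96%)

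*Protocol article*

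**What the plan says.** The primary outcome is stated the same way in the Abstract, the Background and its own section: "The primary outcome measure is the percentage of time spent in hyperoxia (SpO_2_ > 96"%).

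The Secondary outcomes section lists four measures: "The secondary outcomes are the percentage of time spent with an oxygen requirement exceeding 30%, the duration of supplementary oxygen treatment", followed by ventilation days and length of neonatal unit stay. Mean FiO2 during hyperoxia is not one of them.

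The Sample size section takes its inputs from an interim analysis of the unit's crossover study:
- The effect is a "reduction in the mean FiO_2_ delivery during hyperoxia from 29.6% (manual oxygen control period) to 24.7"%, that is 4.9 percentage points of FiO2.
- The spread is given as follows: "The standard deviation for the FiO_2_ requirement of the infants at the beginning of the automated oxygen control period was 4.7"%.
- The conclusion is "Randomisation of 40 infants allowed to detect a difference in the mean FiO_2_ delivery during hyperoxia of 4.9% with a 90% power".

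For time in hyperoxia, the Background reports only a p-value of 0.006 from the crossover study. It gives no mean, difference or SD.

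**The concern.** A sample-size statement should tell the reader what difference in the primary outcome the trial can reliably detect. This one answers that question for another variable. Mean FiO2 during hyperoxia is an oxygen concentration averaged over selected periods. Percentage of time with SpO2 above 96% is a share of the recording. They have different units, spreads and distributions, and the article gives no argument that a standardised effect on one implies a similar effect on the other.

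The two inputs do not match each other either. The effect is for FiO2 during hyperoxia, whereas the SD is for the FiO2 requirement at one time point.

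What is at stake is how the result can be read. If the primary comparison shows no difference, nothing in the plan says how large an effect the trial could have missed.

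**Working it through.** **Inputs**
- Difference 4.9 and SD 4.7, both in percentage points of FiO2 (Sample size).
- Power and alpha: "with a 90% power at the 5% significance level" (Sample size). Sidedness is not stated, so two-sided is assumed.
- Allocation: "Infants are allocated to parallel groups in a 1:1 ratio" (Methods). With 40 infants this is 20 per arm.
- Test: Student's t, or Mann–Whitney if the data are skewed (Statistical analysis).

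**Step 1: reproduce the stated figure.**
Standardised difference: d = 4.9 / 4.7 = 1.043.
Normal approximation: n per arm = 2 × (1.960 + 1.282)² / d² = 2 × 10.51 × (4.7/4.9)² = 19.3, rounded up to 20 per arm, 40 in total.
Power at 20 per arm is 90.9% by the normal approximation and 89.5% by the noncentral t. A one-sided test would need only 16 per arm (32 in total), so the two-sided assumption fits the stated 40. The plan's number is correct for the FiO2 variable.

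**Step 2: what 20 per arm can detect in any approximately normal outcome.**
Solving the noncentral t power equation (38 degrees of freedom, two-sided 5%) for d:
- 90% power: d = 1.05 SD
- 80% power: d = 0.91 SD

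The stated 90% therefore holds for the primary outcome only if the true effect on percentage of time with SpO2 above 96% is itself about 1.05 between-infant SDs. The article does not say so.

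**Step 3: can the document supply that effect?**
No. The p-value of 0.006 for time in hyperoxia comes from a within-infant comparison. The article gives neither that study's sample size nor any SD, so neither a difference nor a between-infant SD can be recovered from it.

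**Step 4: range under assumed values.**
The SDs and differences below are illustrations and do not come from the document. Detectable difference = 1.052 × SD (90%) or 0.909 × SD (80%); power is by noncentral t.

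| Assumed SD (points of % time) | Detectable at 90% | Detectable at 80% | Power if true difference is 10 points | Power if 15 points |
|---|---|---|---|---|
| 10 | 10.5 | 9.1 | 87% | >99% |
| 15 | 15.8 | 13.6 | 54% | 87% |
| 20 | 21.0 | 18.2 | 34% | 64% |
| 25 | 26.3 | 22.7 | 23% | 46% |

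Power runs from 23% to above 99% across this grid, so the document fixes neither its size nor the direction of its departure from 90%.

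**Step 5: the planned alternative test.**
For normal data, Mann–Whitney has a relative efficiency of about 0.955, which takes the Step 1 power from 89.5% to 88.0%. A bounded percentage may well be skewed. The 1.05 and 0.91 SD figures would then no longer apply exactly, and the change could go either way.

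**The case against.** The strongest defence is that the article is open about what it powered. It names the variable and never describes 90% as the power for time in hyperoxia. That is right. A reader might infer that the protocol makes a false power claim for its primary outcome, but the text does not support that. It gives no power for the primary outcome at all.

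A reader might also infer that the trial is underpowered. The document does not support that either: without a mean, difference or SD for time in hyperoxia, true power could lie on either side of 90%.

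A third inference is that the unit already holds the right inputs. The crossover study did measure time in hyperoxia, but only its p-value is shown. The Discussion itself says that study was limited by its crossover design, its monitoring periods and the infants' rather low oxygen need. An SD from it may not carry over to recording until successful extubation.

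Finally, the Background states "our hypothesis that the use of CLAC will reduce the overall duration of oxygen treatment", and no power is given for that. Duration is consistently listed as secondary, and secondary outcomes are commonly not powered, so this is not a fault in itself.

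What remains after these objections is the mismatch. The sole justification of 40 infants concerns a variable outside the outcome list, with an SD from yet another quantity. This is not a detail left to an analysis plan or a fuller protocol, because the paragraph gives effect, SD, power, alpha and sample size in full, for the wrong variable.

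**Conclusion.** The point holds as a mismatch; the arithmetic is not in error. The 40 infants and 90% power reproduce for a 1.04 SD difference in FiO2 and for nothing else in the plan. For the primary outcome the power is unsupported and cannot be determined from the document. What can be said is that 20 per arm detects about 1.05 SD with 90% power and 0.91 SD with 80%. This assumes a two-sided 5% t-test, approximately normal data and all 40 infants contributing. The sample-size paragraph needs correcting. The document gives no ground for saying that the trial is too small or that its analysis is biased.

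**What to change.** Keep 40 infants and rewrite the sample-size paragraph:

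1. Say that the 90% figure relates to mean FiO2 during hyperoxia, was used to set the sample size, and does not apply to the primary outcome.
2. State the detectable difference for percentage of time with SpO2 above 96%: about 1.05 SD at 90% power and 0.91 SD at 80%, for 20 per arm, two-sided 5% t-test, approximately normal data. Add that a Mann–Whitney analysis of skewed data would differ.
3. Convert this to percentage points with a between-infant SD of time in hyperoxia, and name the source. The unit's earlier crossover study may serve if that SD is available, with a note on its short monitoring periods and low oxygen requirement. Otherwise give a range of SDs labelled as assumptions.
4. Say whether a difference of that size is plausible and would matter, so that a null result can be read against it.

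Do not add mean FiO2 during hyperoxia as an outcome merely because it was the quantity powered. It is measured only during hyperoxia after randomisation, which the intervention is meant to reduce. It would therefore compare the arms over selected periods and be undefined for an infant with no hyperoxia.

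The cost is one reworded paragraph, with no extra infants and no new data collection. The stated power may look less favourable than 90%.

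### The half-sample interim has a significance trigger but no threshold, named outcome or stated consequence; if acted on at 0.05, it raises one outcome's type I error to about 8.3%

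*Protocol article*

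**What the plan says.** All the relevant text is in the Sample size section of the protocol article. The calculation is for 40 infants "with a 90% power at the 5% significance level". The next paragraph says that the Ethics committee asked for an interim analysis, to be done "after half the sample have been recruited to review if enough data have been gained at that point". A researcher from outside the project performs it. On disclosure, the article says: "The research team will be blinded to the results of the interim analysis unless there are any significant findings".

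The Statistical analysis section names the tests (Student's t or Mann-Whitney U, and Fisher's exact test for categorical data). It does not mention the interim look or any adjustment of the final level. The outcome sections list one primary outcome, the percentage of time with SpO2 above 96%, and four secondary outcomes.

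**The concern.** Findings can be significant only if the arms have been compared by a test. Asking whether the data already suffice suggests that recruitment might end at that point. Taken together, the two sentences describe a comparative look that could alter the trial. The trigger is bare significance on any finding, next to one undivided 5% level. An analyst who followed the text literally would test at 0.05 at 20 infants and again at 40.

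Two things are at stake. The first is the error rate behind the trial's main claim. The second is the size of the reported effect, because a small trial stopped when it crosses a lenient threshold tends to stop on a high estimate. Disclosure adds a smaller concern: the trial is open, and the research team that would see the results also enrols infants.

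**Working it through.** **Inputs from the article.** The difference is 4.9 percentage points ("that is a difference of 4.9") and the SD is 4.7 ("at the beginning of the automated oxygen control period was 4.7"). Both refer to FiO2: the difference is in mean FiO2 during hyperoxia, which is not the primary outcome. Power is 90%, the level is 5%, allocation is 1:1 and the total is 40. The interim is at half the sample, so 20 infants or about 10 per arm, an information fraction of 0.5. Sidedness is not stated.

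**Step 1: reproduce the sample size.** n per arm = 2 × (z for alpha + z for power)² × (SD/difference)². With two-sided 5%, this is 2 × (1.960 + 1.282)² × (4.7/4.9)² = 19.3, rounded up to 20 per arm or 40 in all, as stated. One-sided 5% would give 16 per arm, or 32, so two-sided testing is inferred. Power at 20 per arm is 90.9% by the normal approximation and 89.5% by the noncentral t distribution. The calculation therefore uses the whole 5% for a single test.

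**Step 2: type I error if both looks use 0.05.** With half the information at the first look, the two test statistics have correlation √(20/40) = 0.707 under the null. The overall error is 1 − P(|Z1| < 1.96 and |Z2| < 1.96) = 0.083. Simulated t tests at 10 and then 20 per arm gave 0.084. This is for one outcome, with a significant interim result counted as a positive trial.

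**Step 3: any of five outcomes.** The article gives no correlations between outcomes, so a range is assumed. Under the null, the chance that at least one of five outcomes reaches p < 0.05 at the interim alone is 1 − 0.95⁵ = 23% if they are independent. It is about 18% with a common correlation of 0.5 and about 13% with 0.8.

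**Step 4: overestimation, for illustration.** The sample-size effect is 4.9/4.7 = 1.04 SD. At that effect, simulated looks at 10 per arm gave p < 0.05 in about 60% of trials, and the mean estimate in those trials was 1.32 SD. That is 1.32/1.04, or about 26% too large. At an assumed true effect of 0.5 SD (not a figure from the article), about 19% were significant, with a mean estimate of 1.10 SD, or 2.2 times the truth. No effect or SD is given for the primary outcome, so its own figures cannot be worked out.

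**Step 5: boundaries that hold 5% overall.** These were solved from the same two-look distribution:

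| Plan | Interim p | Final p |
|---|---|---|
| O'Brien-Fleming | < 0.0052 | < 0.048 |
| Pocock | < 0.0294 | < 0.0294 |
| Haybittle-Peto | < 0.001 | < 0.0498 |

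Leaving the Haybittle-Peto final level at 0.05 gives 0.0502. With simulated t tests at these small numbers, O'Brien-Fleming gave a type I error of about 0.051. At 1.04 SD, simulated power was 0.893 for O'Brien-Fleming and 0.895 for the fixed design; Haybittle-Peto was indistinguishable from the fixed design.

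**The case against.** The strongest objection is that the article sets no 0.05 interim threshold and does not say that a significant result stops the trial or supports a claim. The one stated consequence is that the research team is no longer blinded. This stands. A reader might infer that the trial's false-positive rate is 8.3%, but the text does not support that as a flat statement. If the look can neither stop the trial nor support a claim, the final test keeps its 5%, and a strict interim threshold such as p < 0.001 would leave it at about 5.0%.

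A second objection is that boundaries are commonly left to the full protocol or the SAP, neither of which is shown. This also stands, so the absence of a boundary is not itself the point. But the article does more than mention a look: it fixes the timing, the purpose, the analyst and the trigger. That trigger is loosely set and covers any finding.

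Third, the 1.04 SD figures belong to mean FiO2 during hyperoxia. That is correct, and they serve here only as illustration.

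Two further inferences go too far. One is that stopping early would leave the duration outcomes almost uninformed; 20 of 40 infants is half the planned information. The other is that only favourable results would be released; the wording covers any significant finding, including harm.

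The independent analyst, the opaque envelopes and the downloading of SpO2 and FiO2 from the ventilators do reduce the risk of bias. They do nothing for type I error.

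**Conclusion.** The point holds in conditional form. The article's trigger has no threshold, outcome or consequence attached, and it stands beside a single 5% level. The figure of about 8.3% rests on three assumptions: one outcome, two-sided 0.05 at each look, and a significant interim result that ends the trial or counts as positive. It rises if any of the five outcomes can trigger, by an amount that depends on correlations the article does not give. It falls back to 5% if the look cannot stop the trial or support a claim. The tendency to overstate the effect applies only if the trial stops on such a trigger. Because the stated purpose leaves early stopping open, the wording should be settled before the look takes place.

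**What to change.** Before any interim data are seen, adopt one of two options.

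1. **Keep a comparative look.** Limit it to the primary outcome, state what follows if the boundary is crossed, and set a formal boundary: O'Brien-Fleming (interim p < 0.0052, final p < 0.048) or Haybittle-Peto (interim p < 0.001, final about 0.05). The independent analyst reports only whether to continue or that the boundary has been crossed. The research team sees no comparative results unless it is crossed.
2. **Drop the comparison.** State that no between-arm efficacy test is done at the interim. The final test then keeps the full 5%.

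The cost is a protocol amendment, which the article says goes to the appropriate body for approval. Since the Ethics committee requested the interim, the change should be agreed with it. For option 1, the power loss is under about 0.5 percentage points at the 1.04 SD of the sample-size calculation (0.893 against 0.895 for O'Brien-Fleming). The loss for the primary outcome cannot be confirmed, because the article gives no effect size for it.
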